### Outcome Measures

Before the intervention (baseline), data on dietary intake, physical activity, anthropometric, and blood pressure measurements, biochemical markers of health, eating behaviors and health perceptions, and SCT mediators of behavioral change were collected. These outcome measures also will be obtained at 3, 6, 9 and 12 months.

### Dietary Intake and Physical Activity Assessment

Participants were taught to accurately complete 4-day food records and the Stanford 7-Day Physical Activity Recall Scale [41]. To ensure accuracy in recording foods and beverage consumption, handouts containing examples of standard serving sizes were provided. Participants recorded all food and beverages consumed for three non-consecutive weekdays and one weekend day before the baseline testing session [35]. Four-day food records will be analyzed using the Nutrition Data System for Research (NDSR) dietary analysis software (Nutrition Coordinating Center, Minneapolis, MN, USA) to estimate average daily dietary intake of total energy (kcal/day), carbohydrate (g/day), protein (g/day), fat (g/day), and fiber (g/day) in addition to intake by food groups (svgs/day).

For seven consecutive days before the baseline testing session, participants recorded the number of hours slept, spent in front of a television or computer screen, and engaged in moderate, hard, and very hard physical activity [35]. Participants wore accelerometers at the waist, wrist, or ankle during all waking hours for seven consecutive days while also recording physical activity to provide an objective assessment of energy expenditure. Approximately 70% of participants in each group wore accelerometers as they were not available for all individuals. Physical activity records will be analyzed by summing total hours of moderate, hard, and very hard activity and dividing by seven to estimate hours of physical activity per day. These records will be further analyzed by converting activities into metabolic equivalents (METs) (hr/d), which will be evaluated as light activity (1-3 METs), moderate activity (>3-6 METs), and vigorous activity (>6 METs) to estimate the number of calories expended per day. Accelerometry data will be analyzed using ActiLife 6.11 (ActiGraph, Pensacola, FL, USA) to estimate the number of calories expended per day, the MET rate per day, and the length of time (minutes) spent in sedentary, light, moderate, vigorous, and very vigorous activities.

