### Statistical Analysis

Baseline characteristics of study participants were characterized using descriptive statistics: mean (SD). Participants in the three intervention groups (Treatment) will participate in five data collection sessions at specified intervals (Time). The Shapiro-Wilk test for normality will be used to test for normality and homogeneity of variance within groups; data will be transformed if necessary. Body weight, BMI, waist : hip ratio, FM, BF%, systolic and diastolic blood pressure, serum insulin, glucose, TC, HDL-C, LDL-C, TG, leptin, adiponectin, and resistin will be analyzed as dependent variables. Baseline variables that differ between groups will be included as covariates in the analysis. Dietary intake of macronutrients as estimated from 4-day food records, estimated energy expenditures, eating behaviors, health perceptions, and ratings of SCT mediators also will be compared among groups. A 3 x 5 (3 treatment groups x 5 time intervals) ANOVA with repeated measures on the time factor will be used to assess differences in outcomes within and between treatment groups over time. The group by time interaction will be examined for differences in time trend among intervention groups. Tukey pairwise comparisons will be used in conjunction with ANOVA to detect differences between treatment groups.

Some attrition is expected, as participants may be unable to comply with the intervention or may choose not to continue participation in the study. Participants who withdraw from the intervention will be asked to complete any remaining data collection sessions, and these data will be included in the statistical analyses (ie, intention-to-treat model). Data also will be analyzed using measurements only from those participants who complete all testing sessions. Statistical tests will be two-tailed with significance set at *P*<.01 to reduce the potential for Type I error. All statistical analyses will be conducted using Statistical Package for the Social Sciences (version 22.0, 2013, IBM Corp, Armonk, NY, USA).

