### Limitations

Results from this study will be limited in generalizability to premenopausal women. Future research should examine pre- and post-menopausal women, as these physiological changes appear to be other critical life stage intervals for weight gain. Weight gain prevention should also be examined exclusively in men, as determinants of and strategies for weight gain prevention may differ between men and women. Further, our results may be limited by the length of the study, as the current intervention is only for one year. Surveys, testing sessions or focus groups following completion of the intervention may be useful in order to garner more information about the feasibility of long-term weight gain prevention. There are limitations with using self-reported dietary intake and physical activity; however, participants have been taught to accurately complete food records, and accelerometry data will be used to validate written physical activity records. Finally, our intervention contains multiple components that address weight gain prevention, and the study design does not allow for examination of independent effects of the different elements of this weight gain prevention intervention. Investigator-designed surveys will be used to assist with determining the effects of individual intervention components.

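### Accelerometer wear site (waist, wrist or ankle) is neither standardised nor handled in the stated analysis, so accelerometer-derived outcomes and the check of written activity records can carry site differences

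*Protocol article*

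**What the plan says.** The section Dietary Intake and Physical Activity Assessment allows three wear sites: "Participants wore accelerometers at the waist, wrist, or ankle during all waking hours for seven consecutive days". The purpose is "to provide an objective assessment of energy expenditure". Coverage is partial: "Approximately 70% of participants in each group wore accelerometers as they were not available for all individuals".

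One processing route is described: "Accelerometry data will be analyzed using ActiLife 6.11 (ActiGraph, Pensacola, FL, USA) to estimate the number of calories expended per day", together with MET rate and minutes in five intensity bands. The same section separately converts the written activity records into METs and then calories, so there are two sources of energy expenditure.

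Outcome Measures repeats the assessments at 3, 6, 9 and 12 months. Statistical Analysis says that "estimated energy expenditures, eating behaviors, health perceptions, and ratings of SCT mediators also will be compared among groups", without naming the source, and gives the model: "A 3 x 5 (3 treatment groups x 5 time intervals) ANOVA with repeated measures on the time factor will be used". Its covariate rule admits baseline variables that differ between groups. Limitations gives the device a second role: "accelerometry data will be used to validate written physical activity records".

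The article does not say how the site was chosen, whether it was recorded, or whether it is kept from visit to visit.

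**The concern.** Waist, wrist and ankle move differently during the same activity, so the same behaviour can give different readings depending on where the device sits. The choice of three sites is a positive design statement, not a detail left out for brevity. By contrast, the anthropometric section does fix the body site for waist and hip measurement.

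Three things are at stake, all confined to the accelerometer data:

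- **Comparison between arms at one visit.** Site adds variance, and the mix of sites can differ between arms by chance.
- **Change within a woman.** If she moves from one site to another, her change score includes the difference between sites.
- **Validation of the written records.** Both sources yield calories per day, so their agreement depends on absolute level. A site offset enters this comparison directly, even if site is balanced across arms and never changes. The validation is also one of the article's answers to the weakness of self-reported activity.

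The covariate rule is weak protection. It could pick up site only if site were treated as a baseline variable and seen to differ between groups, and it cannot deal with a change of site after baseline.

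**Working it through.** The article gives no sample size, effect size or site effect for activity, so there is no figure to reproduce. What follows is a sensitivity calculation.

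**From the article**
- Women with baseline data: 81 (Results). Device share: about 70%. Wearers: 0.70 × 81 = 56.7, about 57.
- Per arm, if the arms are equal: 56.7 / 3 = 18.9, about 19. As a check, the 49 women (89%) still enrolled in the two intervention groups imply 49 / 0.89 ≈ 55 at the start, hence 81 − 55 = 26 controls. That gives 0.70 × 55 = 38.5 and 0.70 × 26 = 18.2 wearers, close to 19, 19 and 18.
- Significance level: two-sided 0.01.

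**Assumed**
- The three sites are used equally, with offsets −d/2, 0 and +d/2. Here d is the full spread between the lowest and highest site, in units of the between-woman SD within a site.
- The correlation between visits, ρ, is 0.6 to 0.7.
- The true difference between arms is 1 SD, for the power illustration only.

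**Single visit**
- Added variance: (2/3)(d/2)² = d²/6.
- Effective sample fraction: 1 / (1 + d²/6).
- Chance offset between two arms, 95% limit: 1.96 × √(2 × (d²/6) / 19).
- Power (normal approximation, one pairwise comparison without Tukey adjustment): Φ(√(19/2) / √(1 + d²/6) − 2.576). With d = 0 this is Φ(3.082 − 2.576) = 69.4%.

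| d (SD) | Variance rise | Effective sample | 95% chance offset (SD) | Power |
|---|---|---|---|---|
| 0.5 | 4.2% | 0.96 | 0.13 | 67.2% |
| 1.0 | 16.7% | 0.86 | 0.26 | 60.9% |
| 2.0 | 66.7% | 0.60 | 0.52 | 42.5% |

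If the share of wearers at the highest rather than the lowest site differed by 20 percentage points between arms, the shift would be 0.20 × d: 0.10 SD for d = 0.5 and 0.20 SD for d = 1.

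**Change from baseline**
- Site kept, additive offset o: (Y₁ + o) − (Y₀ + o) = Y₁ − Y₀. The offset cancels and the variance does not rise.
- Site redrawn at random at each visit (the worst case): variance ratio = 1 + (d²/3) / (2(1 − ρ)).
  - d = 0.5, ρ = 0.6: 1 + 0.083 / 0.8 = 1.10
  - d = 1, ρ = 0.7: 1 + 0.333 / 0.6 = 1.56
  - d = 1, ρ = 0.6: 1 + 0.333 / 0.8 = 1.42
  - d = 2, ρ = 0.7: 1 + 1.333 / 0.6 = 3.22

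**Validation against written records**
- Two women with identical true expenditure and identical records, one at each extreme site, differ in agreement by the full d.
- If site is unrelated to the written record, the correlation between the two sources is multiplied by 1 / √(1 + d²/6): 0.98, 0.93 and 0.77 for d = 0.5, 1 and 2. No imbalance or switching is needed.

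**The case against.** The strongest reply is that this is a condensed journal article. A site record, a same-site instruction and site-specific software settings could all sit in a full protocol or device manual that is not shown. A reader might infer that readings from the three sites are pooled. The article never says so, and the inference rests only on the absence of any handling by site. That part of the reply stands. It does not remove the point, because the three permitted sites and the model without a site term are both stated.

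Second, a reader might infer that the arms will be compared with bias, or that the objective activity outcome is uninterpretable. The article supports neither. Bias between arms needs site use to differ by arm, and bias within a woman needs her site to change. Neither is reported. With site kept constant, an additive offset drops out of the group-by-time interaction that the plan tests. This stands too, with two limits. Minutes in intensity bands depend on thresholds, so a site effect there need not be an additive constant. And the cancellation does nothing for agreement with the written records.

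Third, the reach is narrow. Accelerometer measures are not among the named dependent variables, and the energy expenditure to be compared may be the recall-based one, which does not depend on wear site. Neither weight hypothesis is touched. This stands, and it limits the point to accelerometer-derived quantities.

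**Conclusion.** The point holds in limited form and is minor. Following the plan as stated, accelerometer-derived calories, MET rate and intensity minutes can carry site noise, chance imbalance between arms, or shifts where a woman changes site. The check of the written records is blurred by site in any case.

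The size is not known from the documents. With equal use and a spread of 0.5 to 1 SD between the extreme sites, the single-visit loss is modest, equivalent to 4% to 14% of the sample. It becomes substantial (14% to 40%) only if the extremes are 1 to 2 SD apart. The change-score ratios of 1.10 to 1.56 (1.42 to 3.22 for the wider spread) require sites to be redrawn at every visit, which nothing in the article suggests. They mark an upper bound, not an expectation.

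**What to change.** - At 3, 6, 9 and 12 months, give devices to the same women, at their baseline site where it is known, and record the site at each visit.
- Process the data with ActiLife settings appropriate to the site.
- Include wear site as a factor in the accelerometer models, for all wearers. If some women do change site, the factor varies over time and needs a mixed model instead of the classical repeated-measures ANOVA.
- Adjust the validation of the written records for site. Fully separate analyses by site would leave only about 57 / 3 = 19 women each.
- State in Statistical Analysis whether the energy expenditure compared among groups comes from the device or from the written records.
- Use the women with an unchanged site only in a sensitivity analysis. Making them the main comparison would select on an event after randomisation and could itself unbalance the arms.

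The cost is small: a line in the visit procedure, one recorded item, and one or two degrees of freedom among about 57 wearers, with no extra devices. The article reports progress at 8 weeks, before the 3-month visit, so at that point all four later visits could still be standardised. The main drawback is that baseline testing is complete, and the baseline site may be unknown for some women. They need an explicit unknown category or a sensitivity analysis.

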### Anthropometric and Blood Pressure Measurements

Baseline standing height (cm) was recorded to the nearest 0.1 cm using a calibrated scale-mounted stadiometer (Seca 700, Hanover, MD, USA). Body weight (kg) was measured using a calibrated scale (Tanita 410GS, Arlington Heights, IL, USA) to the nearest 0.1 kg. BMI (kg/m^2^) was calculated using height and body weight measurements. A retractable measuring tape (Gulik II, Country Technology, Inc, Gay Mills, WI) was used to measure waist (cm) and hip (cm) circumferences, in duplicate, to the nearest 0.1 cm according to standard protocol [34]. Waist circumference was measured at the narrowest point of the waist, approximately one inch above the navel, and hip circumference was measured at the widest part of the buttocks [35]. Waist and hip circumference measurements were averaged to obtain a single value for each site; these values were used to calculate the waist:hip ratio. Fat mass (FM; kg) and body fat percentage (BF%) were measured using a Tanita scale (410GS).

Seated systolic and diastolic blood pressures (mm Hg) were measured by a trained study investigator using a standard sphygmomanometer (Baumanometer® Desk Model, Copiague, NY, USA) following a 5-minute rest period. Blood pressure measurements were taken in duplicate with a 2-3-minute rest period between readings; mean systolic arterial pressure values and diastolic arterial pressure values will be used in data analyses. Resting heart rate was also measured after the 5-minute rest period.

### Biochemical Markers of Health

Venous blood samples (~30 mL) were collected by a trained phlebotomist between 7:00 to 9:30 AM after a 12-hour fast. Whole blood samples were processed and stored at -80⁰C. Serum will be analyzed for concentrations of insulin, glucose, total cholesterol, high-density lipoprotein-cholesterol (HDL-C), low-density lipoprotein-cholesterol (LDL-C), triacylglycerides (TG), leptin, adiponectin, and resistin.

Serum insulin (µU/mL) (LINCO Research, St Charles, MO, USA) will be measured using enzyme-linked immunosorbent assay (ELISA), and serum glucose (mg/dL) (Stanbio Labs, Boerne, TX, USA) will be measured by spectrophotometry. Total cholesterol (mg/dL), HDL-C (mg/dL) and TG (mg/dL) concentrations will be measured by spectrophotometry using the total cholesterol, HDL-C and TG kits, respectively (Stanbio Labs). Total cholesterol, HDL-C and TG concentrations will be used to calculate LDL-C concentration (mg/dL) using the equation: LDL-C=total cholesterol - HDL-C - (TG/5) [42]. Serum leptin (ng/mL), adiponectin (ng/mL), and resistin (ng/mL) will be measured using ELISA (R&D Systems, Minneapolis, MN, USA). All serum samples for each biomarker will be analyzed in duplicate at corresponding study intervals. Intra- and inter-assay coefficients of variations (CV) are <15% for all kits.

### Eating Behaviors, Health Perceptions, and SCT Mediators of Behavioral Change

Participants completed questionnaires designed to evaluate eating behaviors, health perceptions, perseverance, and SCT mediators. The Eating Inventory [43] will evaluate ratings of cognitive eating restraint, hunger, and disinhibition. The Short-Form 36 Health Survey (SF-36) [44] will assess self-reported health issues. Perseverance will be examined using the Short Grit Scale (Grit-S) [45], and an investigator-designed questionnaire will evaluate SCT mediators, including self-efficacy, outcome expectations, self-regulation, and social and family support. Standard scoring and interpretation methods will be used to evaluate all questionnaires [43-45].

### Statistical Analysis

Baseline characteristics of study participants were characterized using descriptive statistics: mean (SD). Participants in the three intervention groups (Treatment) will participate in five data collection sessions at specified intervals (Time). The Shapiro-Wilk test for normality will be used to test for normality and homogeneity of variance within groups; data will be transformed if necessary. Body weight, BMI, waist : hip ratio, FM, BF%, systolic and diastolic blood pressure, serum insulin, glucose, TC, HDL-C, LDL-C, TG, leptin, adiponectin, and resistin will be analyzed as dependent variables. Baseline variables that differ between groups will be included as covariates in the analysis. Dietary intake of macronutrients as estimated from 4-day food records, estimated energy expenditures, eating behaviors, health perceptions, and ratings of SCT mediators also will be compared among groups. A 3 x 5 (3 treatment groups x 5 time intervals) ANOVA with repeated measures on the time factor will be used to assess differences in outcomes within and between treatment groups over time. The group by time interaction will be examined for differences in time trend among intervention groups. Tukey pairwise comparisons will be used in conjunction with ANOVA to detect differences between treatment groups.

Some attrition is expected, as participants may be unable to comply with the intervention or may choose not to continue participation in the study. Participants who withdraw from the intervention will be asked to complete any remaining data collection sessions, and these data will be included in the statistical analyses (ie, intention-to-treat model). Data also will be analyzed using measurements only from those participants who complete all testing sessions. Statistical tests will be two-tailed with significance set at *P*<.01 to reduce the potential for Type I error. All statistical analyses will be conducted using Statistical Package for the Social Sciences (version 22.0, 2013, IBM Corp, Armonk, NY, USA).

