## Methods

### Recruitment, Screening, and Enrollment

Participants were recruited by word-of-mouth, electronic mail messages, and posted flyers from the University of Illinois campus and the Urbana-Champaign (IL, USA) communities. A flow diagram of response, screening, and randomization steps is displayed in Figure 1. A total of 330 women responded to recruitment methods, between June and August 2014. Of these, 266 women met prescreening criteria (appropriate age, body mass index [BMI], and desire to prevent weight gain) and received screening materials including a medical history form, Zung Self-Rating Depression Scale/Status Inventory [33], and informed consent. A total of 146 women returned screening materials, which were reviewed by investigators. One hundred two women met eligibility criteria for participation, and 87 women were randomized, with 81 women completing baseline testing.

The current study included premenopausal women between the ages of 18-45 years with a BMI of >18.5 kg/m^2^. There were no additional criteria for body weight and BMI to ensure participation by women from a range of weight status categories. Further inclusion criteria included eumenorrhea (≥8 menstrual cycles/year), score of <50 on the Zung Self-Rating Depression Scale/Status Inventory [33], and no self-reported metabolic, cardiovascular or musculoskeletal diseases or use of medications or supplements to manage a chronic health condition. Exclusion criteria included women who currently smoked, were pregnant or attempting to become pregnant or were currently lactating. Women using medications influencing weight regulation, such as steroid or thyroid hormones or oral contraceptives, were excluded if use was for <2 months before the start of the study. Gastric bypass surgery was also an exclusion criterion.

The Institutional Review Board (IRB) for the protection of human subjects at the University of Illinois at Urbana-Champaign (UIUC) approved the study protocol (UIUC IRB#14397). Each participant provided written informed consent before study participation.

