### Study Design

The current study is a 12-month parallel-arm weight gain prevention randomized controlled trial. After enrollment, women were randomized to one of three intervention groups: (1) weight gain prevention intervention delivered by a registered dietitian (RDG); (2) weight gain prevention intervention delivered by a counselor (CSG), or (3) wait-list control (CON) group. The RDG and CSG weight gain prevention interventions are identical in materials and content; the only difference is the credentialing of the individuals leading the intervention. Women in the CON group receive no intervention; upon completion of the 12-month waiting period, these women will be randomized to the RDG group or CSG group and will receive the respective intervention for the next 12-month period.

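### Covariates are chosen by observed baseline differences, so the model depends on chance and an unstated threshold, and adjustment for each outcome's own baseline is not guaranteed

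*Protocol article*

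**What the plan says.** All of this is in the protocol article.

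- **Covariates** (Statistical Analysis): "Baseline variables that differ between groups will be included as covariates in the analysis". The article gives no test or threshold for a difference and no list of candidates. It names no covariate in advance.
- **Model** (Statistical Analysis): "A 3 x 5 (3 treatment groups x 5 time intervals) ANOVA with repeated measures on the time factor will be used".
- **Visits** (Outcome Measures): after the baseline collection, "These outcome measures also will be obtained at 3, 6, 9 and 12 months". The five time levels are therefore baseline plus four follow-up visits, and baseline enters the model as a response.
- **Tests** (Statistical Analysis): "The group by time interaction will be examined for differences in time trend among intervention groups", and "Tukey pairwise comparisons will be used in conjunction with ANOVA to detect differences between treatment groups".
- **Level** (Statistical Analysis): "Statistical tests will be two-tailed with significance set at *P*<.01 to reduce the potential for Type I error". The text does not say that this level governs the baseline comparison.
- **Allocation** (Study Design): "women were randomized to one of three intervention groups". Under Recruitment, Screening, and Enrollment: "87 women were randomized, with 81 women completing baseline testing".

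**The concern.** After randomization, a baseline difference between arms is a chance event. A rule that admits covariates because they differ selects on imbalance, when what makes a covariate useful is how well it predicts the outcome. Two things follow.

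First, the set of covariates, and so the adjusted estimate, depends on the random allocation and on a cut-off that nobody has stated. Different outcomes could end up with different models for no scientific reason.

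Second, the best available predictor of most outcomes is their own baseline value. Under this rule it becomes a covariate only if it happens to differ. If it does, it stands in the model both as a covariate and as the first of the five responses, which is incoherent.

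At stake are precision and protection against regression to the mean when an outcome starts out imbalanced. Both can be had almost free, because the baseline values are already collected.

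**Working it through.** The article states no power or precision figure, so there is none to reproduce.

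**Inputs from the article.** 81 women have baseline data. The Results report 49 women (89%) still enrolled in the two intervention groups, and 49/0.89 ≈ 55, which leaves 81 − 55 = 26 controls, or about 27 per arm. The Statistical Analysis section names 16 dependent variables, from body weight to resistin. Table 1 gives a baseline weight of 76.1 kg (SD 19.0). The Discussion's ±3% success criterion is 0.03 × 76.1 ≈ 2.3 kg.

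**Assumptions.** Correlations between visits (r or ρ), the threshold for a baseline difference, independence of the 16 variables, and a 28/27 split of the 55.

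**1. Chance selection.** P(at least one of 16 differs) = 1 − (1 − a)^16.
- a = .05: 1 − .95^16 = .56, with 16 × .05 = 0.8 expected.
- a = .01: 1 − .99^16 = .15, with 16 × .01 = 0.16 expected.

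For any single outcome, its own baseline would be selected in about 5% of trials at a .05 threshold.

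**2. Precision at one follow-up visit.** A change score has variance proportional to 2(1 − r), and baseline-adjusted analysis (ANCOVA) to 1 − r². The ratio is (1 − r²)/[2(1 − r)] = (1 + r)/2, and the equivalent sample-size factor is 2/(1 + r).
- r = 0.5: ratio 0.75, factor 1.33.
- r = 0.7: ratio 0.85, factor 1.18.
- r = 0.97: ratio 0.985, factor 1.015.

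**3. Weight, pairwise difference between arms.** SE = 19.0 × √(2v/27), with equal correlation ρ between all visits. The multiplier v is 2(1 − ρ) for change, 1 − ρ² for ANCOVA at one visit, (1 + 4ρ)/5 for the unadjusted mean of all five visits, and (1 + 3ρ)/4 − ρ² for ANCOVA on the mean of the four follow-up visits.

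| ρ | Change, one visit (kg) | ANCOVA, one visit (kg) | Unadjusted mean of five (kg) | ANCOVA, mean of four (kg) |
|---|---|---|---|---|
| 0.5 | 5.17 | 4.48 | 4.01 | 3.17 |
| 0.7 | 4.01 | 3.69 | 4.51 | 2.76 |
| 0.95 | 1.64 | 1.61 | 5.07 | 1.27 |
| 0.98 | 1.03 | 1.03 | 5.13 | 0.81 |

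For change in weight, ANCOVA adds almost nothing at high ρ. For group means averaged over visits, the usual target of Tukey comparisons on the group factor, the loss is large at every ρ shown.

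**4. Error rates under the null.** 12,000 simulated trials per ρ, arms of 28/27/26, equal correlation, nominal .05. The rule is applied to the outcome's own baseline with an assumed threshold of .05.

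| Test | ρ | All trials | Baseline p < .05 | Baseline p .05 to .20 |
|---|---|---|---|---|
| Group main effect under the rule | 0.7 | .024 | .044 | .114 |
| | 0.95 | .013 | .067 | .064 |
| Group by time, unadjusted | 0.7 | .050 | .103 | .071 |
| | 0.95 | .050 | .047 | .050 |
| ANCOVA fixed in advance | 0.7 | .052 | .044 | .056 |
| | 0.95 | .050 | .067 | .047 |

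The column for baseline p < .05 rests on about 600 trials per row, a Monte Carlo SE near √(.05 × .95/600) = .009, so .067 is not clearly different from .05. At nominal .01 the main effect under the rule rejects in .0023 (ρ 0.7) and .0005 (ρ 0.95) of trials.

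If the outcome's own baseline is a candidate and the threshold is .05, trials in the p < .05 column would be adjusted, and the exposure lies in the near-miss column. With a stricter threshold, some of the p < .05 trials would also stay unadjusted. At ρ = 0.5, unadjusted tests in imbalanced trials rejected about .14 of the time.

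**5. Baseline as both covariate and time level.** Separate null simulations with the same arm sizes and correlation structure gave uncorrected group by time error between .047 and .058 when both uses were forced, and between .045 and .051 when baseline entered only by the rule (nominal .05).

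**The case against.** The strongest reply is that the hypotheses concern weight over 12 months, and the group by time interaction already addresses that. Baseline is one of its levels, so the test works on change and baseline is not ignored. For weight the further gain from adjustment is about 1.5% in variance at r = 0.97. This stands, and it means the point bears mainly on the secondary outcomes and on group means averaged over visits.

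Three stronger readings are tempting, and the article does not support them.

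- A reader might infer that the rule inflates type I error. It does not do so overall: group by time stays near nominal and the group main effect is conservative. The raised rates are conditional on chance imbalance and appear mainly at lower correlations. The selection also uses baseline data only, not follow-up outcomes.
- A reader might infer that using baseline twice distorts the group by time test. The simulations show no such distortion of its overall error. The article also does not say that an outcome's own baseline is a candidate covariate.
- A reader might infer that about two covariates would enter by chance for each pair of arms. That needs roughly 40 candidates tested at .05 (40 × .05 = 2). Neither figure is in the article, and at its only stated level, .01, the same count gives 0.4.

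The (1 + r)/2 ratio is for a single follow-up visit and does not describe the full five-visit model. The article supplies no correlations, so the 0.75 to 0.85 range is illustrative.

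A separate analysis plan might add detail, but that is no answer here: the article does not leave covariates open, it fixes the rule.

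**Conclusion.** The point holds as a low-cost improvement. The article commits the trial to choosing covariates by chance imbalance against an unstated threshold, and does not guarantee adjustment for each outcome's own baseline. On the 16 named outcomes alone, the chance that at least one triggers the rule moves from 15% to 56% as the threshold goes from .01 to .05.

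The harm is lost precision and weaker protection against regression to the mean, not a raised overall false-positive rate. At a single visit it is negligible for change in weight and material for less stable outcomes, such as serum markers and questionnaires may be. For group means averaged over visits it is larger: at ρ = 0.7, an SE of 4.51 kg against 2.76 kg for weight.

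The sizes rest on the assumed correlations, equal correlation between visits, independence of the 16 outcomes and approximate arm sizes. The case against selecting on imbalance rests on none of these; it follows from randomization.

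**What to change.** Replace the covariate sentence in Statistical Analysis with: *Each model adjusts for the baseline value of the outcome analysed, and any further covariates are prognostic variables named before outcome data are analysed, regardless of observed imbalance.*

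Model the 3, 6, 9 and 12 month values with baseline as a covariate, so that baseline is no longer also a level of the time factor. A longitudinal model that keeps baseline as a response, with group means constrained to be equal at baseline, is equally acceptable.

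The cost is wording and one or two degrees of freedom. No new data are needed, since baseline values of the outcomes are already collected.
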